## Visit 1 - Pre-randomisation phase

Once potential participants have been identified through their responses on the MDQ, they will be invited to the NIHR-CRF for a pre-randomisation phase visit. The pre-randomisation phase visit is expected to last approximately 6 hours and will take place no sooner than 2 weeks prior to randomisation.

At this visit, participants will be presented with a hard copy of the Information Sheet and will be able to discuss the details of the study with the researcher. They will also be given a letter which outlines the details of the services that are available should they feel concerned about their mood. Participants will be given time to consider the information and decide whether they will participate in the study. Written informed consent will then be obtained.

Participants will be screened using the MINI by a researcher or clinician. We anticipate that a subset of participants will meet axis I/II criteria. Regardless of whether they meet axis I/II criteria, the researchers will then ensure that all participants meet the study inclusion and exclusion criteria. Only those that meet the inclusion and exclusion criteria will be eligible to take part in the study (see 7.2 and 7.3).

After assessment of eligibility, participants who meet the study criteria will undergo a research assessment which includes collecting demographic information, clinical history (including duration of illness, previous use of psychotropic medicines, family history of mood disorders, concomitant medication and a physical examination, including being asked to take a pregnancy test. Participants will be asked about past substance use and encouraged to refrain from substance use during the study. The Alcohol Used Disorders Identification Test (AUDIT) will be completed and participants encouraged to limit alcohol consumption to 14 units per week for females and 21 for males. Participants will also be asked to complete short state and trait questionnaires on an IPad, including the Barratt Impulsiveness Scale (BIS), Sleep Condition Indicator, Morningness-Eveningness Questionnaire (MEQ), Maclean Screening Instrument, Affective Lability Scale (short-form), and Affect Intensity Measure. In addition they will also complete screening tools for comorbid borderline personality disorder [Zanarini, 2003] and attention deficit hyperactivity disorder (ADHD) [Adler 2006]. These are all short self-report questionnaires. Participants will be given an e-patch ECG monitor and an actigraphy watch to wear. They will also be given an iPad and instructed on how to complete the daily (PANAS) and weekly (True colours) mood ratings and cognitive tasks.

Blood samples will be taken at this visit and sent for analysis.

A letter will be send to the participants GP informing them that the individual is planning to take part in the study.

## 8.4. Visit 2 - Randomisation

The randomisation visit will take place approximately 2 weeks after study entry.

During this visit eligibility for the randomised phase will be checked including continued consent, absence of contraindications to nicardipine including pregnancy, adherence to cognitive tasks and any current medication. Any difficulties will be explored and, if possible, overcome to enable the participant to continue in the study.

Eligible participants will be entered into the randomised phase (see below 8.5) and provided with study medication. Participants will complete MRI scan and MEG brain scans at this visit prior to taking any study medication. Participants will be asked to arrive for the scans wearing metal free clothes and no make-up. However, changing room facilitates and make up remover are available for participants to prepare on site. The scans will take place at the Oxford centre for Human Brain Activity (OHBA) at the Department of Psychiatry on the Warneford Hospital Site. Participants will be screened for exclusion criteria for scanning again by the radiographer and asked to check for metal. They will also be asked to complete mood ratings before being positioned in the scanner and anatomical and functional scans will be run. They will be asked to rest with their eyes open for part of the time and also to perform simple cognitive tasks involving detecting visual (via screen projection) stimuli and making choices using button-pads or grip-force transducers. The scanners will be operated by a trained radiographer/scanner operator and the task will be administered by a trained researcher. A similar procedure will be followed for the MEG scan. During the MEG scanning eye movements will be tracked. Patients will be in each scanner for no more than 2 hours. Undergoing both scans and completing the cognitive tests will take about 5 hours in total either at a single visit or over 2 visits in close proximity.

At this visit participants will be provided with an e-Patch and asked to wear it for 72 hours, followed by the completion of a sleep questionnaire and a sleep diary. They will be given a portable blood pressure monitor to monitor their blood pressure throughout the two week randomisation phase . Dates for the final study visit and the second MRI and MEG scans will be provided.

A letter will be send to the participants GP informing them that the individual has been randomised to nicardipine or placebo

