# OBJECTIVES AND OUTCOME MEASURES/ENDPOINTS

| **Objectives** | **Outcome Measures/Endpoints** |
| --- | --- |
| Primary objective:   - To compare the effects of nicardipine and placebo on measures of cognitive instability.   . | Primary outcome measure:   - Cross sectional and longitudinal assessments of cognition |
| Secondary objective:   - To compare the effects of nicardipine and placebo on variability in neural dynamics during MRI and MEG scans. This will include scans during resting state and whilst performing neuropsychological tasks. - To explore the effects of nicardipine on physical activity and sleep. - To develop a profile of calcium channel expression and calcium signalling with and without nicardipine treatment - Heart rate variability - Mood instability | Secondary outcome measure:   - Blood oxygen level dependent signal during rest and during cognitive testing; induced and evoked field activity - Activity monitor measurements:   2a. Actigraphy data from a maximum of two wearable units, allowing analysis of indices of:   1. Frequency and amplitude of movements during daytime activity   ii. Categorisation of activity types.   1. Duration, timing, and quality of sleep.   2b. Sleep quality indicator questionnaire (SCI; self-report sleep measure (Espie, 2014)).   - Measure effects of nicardipine on leucocyte calcium channel expression and calcium signalling - Change in R-R interval variability - Change in mood instability using root mean square of the successive differences (RMSSD) |

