## Visit 3 – Final visit:

At approximately 2 weeks post-randomisation participants will be asked to attend a final study visit. At this visit, vital signs will be checked, and ECG and blood samples will be repeated. Participants will also complete a second battery of cognitive tasks. All equipment will be returned at this visit including medication bottles and any remaining medication. A post-treatment MRI scan and MEG scan will be done. If possible, post randomisation scans and the final week 2 visit will be carried out on the same day. If this is not possible due to scanner availability, separate visits will be scheduled at the convenience for the participant.

At this visit checks of adherence and for adverse events will be carried out.

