## Description of procedure

***Daily cognitive tasks***. Participants will be asked to complete a battery of neuropsychological tests on a computer. They will also be provided with an iPad with pre-installed apps to enable them to complete short cognitive assessments (Appendix E) plus the PANAS questionnaire twice daily. They will be shown how to use the apps and asked to respond to prompts to complete cognitive assessments for the duration of the study. Data from the apps will be sent wirelessly and electronically to a secured server for analysis.

Participants will be informed that they are able to contact the Research Team during working hours should they have any concerns or if they experience any problems with the iPad or activity monitor(s) (see Appendix F: *Theme 3*).

Imaging interventions: Participants who need optical correction will be asked for details of their current spectacle prescription so that researchers can check whether they will be able to provide MRI/MEG compatible glasses for that prescription (Appendix E).

***Sleep, motor activity and social interactions*.** Participants will be given an activity monitor (GeneActiv wrist-worn accelerometer) and asked to wear it as much as possible from entry into the study until the end of the randomised phase. Participants will be provided with instructions on how to use the monitor and data will be stored on the device itself .

Participants will be given a copy of the Sleep Condition indicator; self-report sleep measure (Espie, 2014), and the Morningness-Eveningness Questionnaire (MEQ) and asked to complete them before wearing the ePatch for 72 hours (see below). Participants will also be asked to keep a sleep diary for the study duration.

***Profile of the calcium signalling system.*** Effects of nicardipine on leucocyte calcium channel expression and calcium signalling will be explored. Participants will be asked to provide blood samples (of approximately 9 teaspoonfuls of blood) pre-calcium treatment at the screening visit and post-calcium treatment at the final visit 2 weeks after randomisation (Appendix G).

***Physiological effects of nicardipine*.** Heart rate and blood pressure will be measured. Participants will also be provided with an e-Patch, shown how to attach it and asked to wear it for a 72-hour period prior to randomisation and 72 hours post-randomisation (Appendix I)**.**

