# NICARDIPINE

## Description

Nicardipine will be provided as Cardene SR 30mg capsules. Cardene SR 30mg capsules will be purchased from Oxford Pharmacy Stores. The Department of Psychiatry will (over-)encapsulate Cardene (to mask print on the capsule) and encapsulate matched placebo tablets. Each bottle will be assigned a unique randomisation number to ensure concealment of allocation.

*Nicardipine dose:* Following random allocation (see 8.6), nicardipine/placebo will be given at a dose of 60mg. This will be a stable dose throughout the study period. Participants will be instructed to take the capsules as two separate doses – one 30mg dose after breakfast and one 30mg dose at bedtime*. Nicardipine takes at least 3 days to reach steady state plasma levels.

* Capsules should be taken as near to 12 hours as possible after the previous dose.

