# Appendix I: ePatches

The ePatch has been designed to provide reliable high quality continuous ECG monitoring for long periods of time without any patient discomfort or impairment of normal daily life activities.

Following recording data can be downloaded via a micro USB and can be visualised and analysed in the same way as ECG’s recorded on traditional equipment.

ePatches consist of a re-usable sensor with a single use electrode. Each electrode provides continuous ECG recording for a 72-hour period

Participants will be asked to wear ePatches for two 72-hour periods during OxCaMS. The first period will be during the pre-randomisation phase. The second period will be after the randomisation visit and before the 4-week visit. At the start of each recording period they will be asked to remain seated for 10 minutes to enable a resting ECG to be recorded.

| **[figure not shown]** | ePatches have an adhesive back which sticks to (hair-free) skin and are placed in the centre of the chest underneath clothing. They can be worn under normal clothing and are shower proof. |
| --- | --- |

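### The second ePatch recording has no fixed start and, on the natural reading, covers nicardipine's build-up; separately booked post-treatment scans may also follow capsule return

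*Protocol*

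**What the plan says.** **Recording.** Sections 6.2 and 8.4 give out the second ePatch at Visit 2 ("At this visit participants will be provided with an e-Patch and asked to wear it for 72 hours"), and Appendix B ticks it under that attendance. Section 8.13 has participants "asked to wear it for a 72-hour period prior to randomisation and 72 hours post-randomisation" and refers to Appendix I. Appendix I is wider: "The second period will be after the randomisation visit and before the 4-week visit". It adds: "At the start of each recording period they will be asked to remain seated for 10 minutes to enable a resting ECG to be recorded".

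**Exposure.** Section 9.1 states: "Nicardipine takes at least 3 days to reach steady state plasma levels". Capsules are taken after breakfast and at bedtime.

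**Outcome.** Section 5 lists "Change in R-R interval variability" as a secondary outcome. Appendix I plans two recordings in all, so only one follows randomisation.

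**Scans.** Section 6.4 says of Visit 3: "All equipment will be returned at this visit including medication bottles and any remaining medication". Post-treatment MRI and MEG are preferred on that day; failing that, "separate visits will be scheduled at the convenience for the participant". Section 6.2 aims for week 4, and Appendix B places the scans at day 28 ±2.

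**The concern.** The recording lasts as long as the minimum time the protocol gives for reaching steady state. Section 8.13 files the ePatch under the physiological effects of nicardipine, so its purpose is to show a drug effect. If it is worn from Visit 2, the only post-randomisation recording is made while levels are still rising, and the resting strip may be drug-free in both arms. If some participants start early and others late, as Appendix I permits, exposure also varies between participants for no planned reason.

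The scans raise a similar timing question at the other end. The pre-treatment scans carry an explicit rule that they precede any study medication. The post-treatment scans carry no rule about capsule return or time since last dose. Both gaps would tend to shrink the between-arm difference on secondary outcomes in a study of 20 per arm.

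**Working it through.** **1. The protocol's own figure.** Minimum time to steady state: 3 × 24 h = 72 h. Recording length: 72 h.
- Started at the first dose: 72 − 72 = 0 h fall at or after the earliest steady state.
- Started 72 h after the first dose (day 4): all 72 h can.

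**2. Resting strip.** Section 8.4 puts the pre-treatment scans at Visit 2 before any study medication, and Appendix I puts the strip at the start of the recording. If the patch is started during Visit 2, the strip can precede the first dose. The expected drug difference on that strip is then zero.

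**3. Size of the build-up (assumption, since no half-life is given).** Take first-order accumulation. Let F be the fraction of plateau counted as steady state and T the time to reach it. Then k = −ln(1 − F)/T, and the mean fraction of steady state over the first 72 h is m = 1 − (1 − e^(−72k))/(72k).
- F = 0.90, T = 72 h: 72k = 2.303; m = 1 − 0.900/2.303 = 0.61
- F = 0.96875 (five half-lives), T = 72 h: 72k = 3.466; m = 1 − 0.969/3.466 = 0.72
- F = 0.90, T = 120 h: 72k = 1.382; m = 1 − 0.749/1.382 = 0.46
- F = 0.96875, T = 120 h: 72k = 2.079; m = 1 − 0.875/2.079 = 0.58

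**4. What that could cost in power.** Section 11.1 claims more than 90% power with 40 participants but gives no effect size or SD, so the claim cannot be reproduced. Back-solving for 20 per arm, two-sided 0.05 and 90% power gives d = (1.960 + 1.282) × √(2/20) = 1.025. If the effect scales with level, power = Φ(1.025 × m × √10 − 1.960).
- m = 0.61 to 0.72: power about 51% to 65%
- m = 0.46 to 0.58: power about 32% to 47%

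**5. Scans after capsule return.** On the same assumptions the fraction remaining t hours after the last dose is (1 − F)^(t/T).
- T = 72 h: about 31% to 46% at 24 h, and 10% to 22% at 48 h
- T = 120 h: about 50% to 63% at 24 h, and 25% to 40% at 48 h

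The Appendix B window would bound the gap between return and scan at 30 − 26 = 4 days.

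**6. Room for a later recording.** The windows in Appendix B allow a shortest interval between Visits 2 and 3 of 26 − 16 = 10 days. Build-up plus recording needs 3 + 3 = 6 days, so a later start fits.

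**The case against.** The strongest reply is that the protocol never says the patch goes on with the first dose. Sections 6.2 and 8.4 say when it is handed out and how long it is worn. Section 4.2 says only that heart rate variability is measured before and during the randomised phase. Appendix I, which section 8.13 cites, gives the wide window. The pairing in section 8.13 may simply name the two phases, since the first patch is given out about two weeks before randomisation. This stands in part. It means the defect is an unfixed start with passages to reconcile, not a proven recording at low exposure. A reader might infer that the whole recording falls in build-up as a matter of fact; Appendix I does not support that.

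On the scans, same-day scanning is preferred, week 4 is the target, and a separate scan day could come before Visit 3. Scanning after capsule return is therefore permitted by silence, not planned. Separate scan days are, however, a real contingency: section 8.5 gives a visit length for them, and the sections on expenses and participant burden provide for them.

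The exposure percentages rest on assumed kinetics. That also stands, which is why they are given as ranges and as illustration only.

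**Conclusion.** The point holds as a timing gap. The protocol sets a 72-hour recording beside a minimum of 72 hours to steady state, gives out the patch at the start of that period, and does not fix when the recording begins. On the natural reading the recording lies wholly in build-up and the R-R difference is attenuated. Mean exposure would be roughly 61% to 72% of steady state, or 46% to 58% if steady state takes 5 days. These figures assume first-order accumulation and a start at first dose. The power figures further assume an effect proportional to level. Post-treatment scans on a separate day may follow capsule return, within the day 28 ±2 window.

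Two stronger conclusions are tempting. One is that a null result on heart rate variability would be uninterpretable; the working shows attenuation, not loss of all signal. The other is that the trial's main result is at risk. The daily cognitive tasks run through the whole randomised phase and are untouched; the outcomes affected (R-R variability, MRI and MEG) are all secondary. This is a worthwhile, low-cost improvement, not a must-fix.

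**What to change.** - **ePatch.** Reconcile sections 6.2, 8.4, 8.13 and Appendix B with Appendix I. State that the second 72-hour recording, including the 10 resting minutes, starts no earlier than day 4 of the randomised phase and finishes before the post-treatment scan day. It should not run up to Visit 3 itself: that is the preferred MRI/MEG day, and the patch must be off for scanning.
- **Scans.** In sections 6.4 and 8.5, require separately booked post-treatment scans to take place on or before the day study medication is returned, and record time since last dose at each scan.

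These changes concern assessment timing only; no change to dose or treatment duration is proposed. Device, wear time and number of visits stay the same. The costs are that participants apply the second patch themselves (section 8.13 already has them shown how), there is less time to repeat a failed recording, and scanner booking is slightly tighter.

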## 8.5. Visit 3 – final visit

In the second week post randomisation, participants will be invited for the final study visit. This visit is expected to take approximately 7 hours including scanning time (if scans are scheduled on a different day due to scanner availability, this visit will take approximately 2 hours and 20 minutes). At this visit, participants will be asked to complete a battery of neuropsychological tests on a computer. Baseline assessments will be repeated at this visit including weight, pulse, blood pressure, current medication, blood tests and ECG.

Participants will be asked to return all of the devices they had been given at the beginning of the study as outlined in the devices agreement signed at the start of the study (see appendix M) Participants will also be asked to return medication bottles, with any remaining capsules.

Post-treatment MRI scan and MEG scans will be completed under the same conditions as those undertaken pre-treatment.

A letter will be send to the participants GP informing them that the individual has completed the study.

## 8.6. Post-study follow-up

Participants will be contacted within a fortnight of study completion, usually by phone, following cessation of study treatment to review the status of any reported Adverse Events and to check for any unreported AEs.

Please see Appendix B for a schedule of procedures during the study duration.

## Randomisation and allocation concealment

Randomisation will be done in according to an algorithm that minimises on one prognostic factor (see 8.8). Each participant will be randomised to either nicardipine or placebo, with participants, clinicians and researchers involved in study recruitment and assessment visits being blind to allocation.

The computer-generated randomisation schedule will be implemented by a trials manager, based at the University Oxford Department of Psychiatry and who is not involved in the study. A non-deterministic minimisation algorithm will be used to produce treatment groups balanced for important prognostic factors. The first 10 participants will be allocated treatment randomly without minimisation to avoid predictability. Subsequently, the minimisation algorithm will be applied with an allocation ratio that is not fully deterministic: there will be an 80% bias in favour of allocations that minimise the imbalance.

## Minimisation variables

The randomisation algorithm will minimise on gender (M, F).

## Unblinding of treatment

A list of current participants showing their allocation will be maintained by Oxford Health pharmacy staff who are designated unblind.

*Emergency unblinding:* Participants will be given a card to carry to say that they are in the study and may be taking nicardipine or matched placebo. Nicardipine is widely used and therefore any medical doctor attending a study participant who is experiencing a medical emergency will be fully aware of its clinical effects. Participants will be made fully aware of any adverse events they may be likely experience. Participants will also be able to access a consultant-led on-call trials rota which operates 24 hours a day, 7 days a week.

*Non-emergency unblinding:* Allocation of treatments will be recorded on a Randomisation List which will be updated when each new participant enters the randomised phase. The list will be held by unblind staff at the Oxford Health pharmacy. These staff will, on the instructions of the Chief Investigator or delegate, access the list and reveal the allocation to an individual participant.

## Sample Handling

*Blood samples:* Blood samples will be taken using standard phlebotomy techniques. Approximately 50ml will be taken. Tests will include urea and electrolytes, full blood count, LFTs, T4, T3, TSH, leucocyte calcium channel gene expression and studies of calcium signalling. A sample will also be taken to measure calcium level using the InSight™ Electrolyte Analyser located in the NIHR-CRF. Weight/BMI, pulse and blood pressure will also be recorded and an ECG will be performed. Samples for calcium assays will be processed in the NIHR-CRF and analysed using the InSight™ Electrolyte Analyser. Some will also be sent to the pathology laboratory at the John Radcliffe Hospital for a validity check. Assays for IL-6 will be done in the Department of Psychiatry Neurosciences Laboratory. All other blood assays will be done at the John Radcliffe Hospital using standard tests.

Blood samples will be used for genotyping for the CACNA1C risk allele.

Participants will be asked to indicate on the Consent Form whether they are willing for samples to be retained for future research. Samples to be retained for future ethically approved research will be stored in a freezer (-18^o^C) in the University of Oxford Department of Psychiatry, the NIHR CRF or the Department of Pharmacology. At the end of the study, samples from participants who consented to gift them for future research will be linked to key clinical information and then anonymised.

